## Abstract

Introduction: Proactive preparedness strategies are more effective than reactive responses in minimizing the negative impacts of health emergencies, including outbreaks. Despite their potential to enhance community resilience, household preparedness initiatives are limited in Malaysia. The focus is primarily on flood disasters, often overlooking marginalized communities, such as indigenous groups. In Selangor, these communities live near forest edges and depend on the forest for livelihood, increasing their risk of exposure to zoonotic and novel threats such as Disease X. They also face challenges such as socioeconomic status, poor living conditions, healthcare barriers, and societal marginalization, making them particularly vulnerable to severe impacts from outbreaks. This study aims to evaluate the effectiveness of X-SIAGA, a newly developed intervention package, in improving household preparedness for Disease X and potential outbreaks among indigenous communities in Selangor, Malaysia.

Methods: This study will be a two-arm, parallel, single-blinded, cluster-randomized trial using multistage and simple random sampling to evaluate the effectiveness of X-SIAGA. The primary outcome is *Household Outbreak Preparedness* scores, with secondary outcomes including *Cognitive Preparedness *scores and *Preparedness Behaviour* scores. District and village clusters will be selected using multistage sampling and randomly assigned interventions via computer-generated numbers. Ninety-six households from eight villages are planned for recruitment, split evenly between the intervention and control groups. The intervention group will receive X-SIAGA along with educational brochures, while the control group will receive only the brochures. Outcome measures will assess changes from baseline to immediately after and one- and three-month post-intervention or control.

Results: As this is a study protocol, results are not yet available. The study is designed to assess changes in *Household Outbreak Preparedness* scores (primary outcome), as well as *Cognitive Preparedness scores* and *Preparedness Behaviour* scores (secondary outcomes).

Conclusion: This protocol describes an intervention study that will generate evidence on the effectiveness of X-SIAGA, a novel, culturally tailored, and theory-based intervention designed to improve household preparedness for Disease X and potential outbreaks among indigenous communities in Selangor.

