In this study, Cognitive Preparedness refers to the mental process of preparedness, specifically the knowledge, attitudes, and health beliefs a person holds regarding readiness for Disease X and outbreaks. Preparedness Behavior refers to the observable actions or practices carried out in preparation for such events. Literature suggests that effective preparedness requires both cognitive and behavioral components. Individuals need to have sufficient knowledge and positive attitudes and health beliefs, and they must also demonstrate these through actual preparedness behaviors [12,13]. Therefore, *Household Outbreak Preparedness* is defined as a continuum that integrates both *Cognitive Preparedness* and *Preparedness Behavior* to best reflect the overall level of preparedness [24]. The theoretical framework is presented in Figure 1, and the conceptual framework is presented in Figure 2.

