\begin{document} m = \frac{(Z_{1-\alpha/2} + Z_{1-\beta})^2 \, 2\sigma^2}{\Delta^2} \left[ 1 + (n - 1)\rho \right] \end{document}

where *m* is the number of households per arm; *Z_1−α/2_* is the standard error associated with a 95% confidence interval (*Z_1−α/2_*=1.96); *Z_1−β_* is the standard error associated with 80% power (*Z_1−β_*=0.842); Δ is the mean awareness score difference between the pre- and post-assessments in the intervention group within a community-based trial on disaster preparedness intervention (Δ=15.97) [26]; σ^2^ is the total variation in awareness score between the pre- and post-assessments in the intervention group within the same trial (σ^2^=138.949) [26]; *n* is the estimated median number of households in Proto-Malay majority Orang Asli villages in Selangor (*n*=54) [18]; and ρ is the intracluster correlation coefficient (ICC) (ρ=0.048) [27].

Allowing for an anticipated attrition rate of approximately 30%, the ideal sample size was set at 45 households per arm. Following the CONSORT Statement recommendation that each study arm should include at least four clusters [28], this study employs multistage sampling to select four Orang Asli villages per arm, aiming for 12 households in each village, a total of 96 households for the study.

Eligibility criteria

Table 2 outlines the eligibility criteria for clusters at both the district and village levels. Meanwhile, Table 3 provides the inclusion and exclusion criteria for participants who will represent their households by participating in X-SIAGA and completing a questionnaire designed to assess the change in preparedness scores at all data collection points.

**Table 2 TAB2:** Eligibility criteria for district and village level clusters.

District	Village
Districts in the state of Selangor.	Villages that have not previously participated in any outbreak preparedness programs.
Districts with gazetted Orang Asli villages.	Villages with more than 12 households.
Districts with more than 5 Orang Asli villages.	Villages accessible via road transport.

**Table 3 TAB3:** Inclusion and exclusion criteria of participants.

Inclusion criteria	Exclusion criteria
Orang Asli descent.	Having physical or cognitive disabilities (e.g., blindness, deafness, schizophrenia and dementia).

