To prevent contamination bias, the study ensures sufficient geographical separation between intervention and control villages to minimize interactions among participants from different groups. Prior to recruitment, the research team held meetings with village leaders and committee members, in the presence of JAKOA officials, to explain the X-SIAGA intervention, emphasize the importance of strict confidentiality, and discourage discussions about the intervention. These leaders and committee members then conveyed this information to eligible participants during household recruitment. All participants will again receive a detailed explanation of the privacy and confidentiality policy when expressing interest in joining the trial, and only those who provide consent will be enrolled. To mitigate attrition bias, the study will employ an Intention-to-Treat (ITT) approach. Additionally, to sustain motivation and engagement, perishable goods will be offered as incentives at each stage of data collection.

Statistical methods

The statistical analysis for this study will be carried out by using the IBM SPSS Statistics for Windows, Version 26 (Released 2018; IBM Corp., Armonk, New York). Descriptive statistics will include frequency and percentages for categorical data and mean and standard deviation for numerical data.

To compare baseline sociodemographic characteristics between the intervention and control groups, a Pearson Chi-Square test will be utilized for categorical variables, while an Independent Samples t-test will be used for continuous variables. To evaluate changes over time from T0 to T3 between and within the groups, a repeated-measures analysis of variance will be conducted. To assess variation in results between and within the groups across the different time points, while also controlling for potential confounding variables, a generalized estimating equation will be utilized.

Statistical analyses will use a two-tailed test to evaluate the superiority hypothesis. The null hypothesis states that there is no difference between the X-SIAGA intervention package and standard educational brochures. A significance level of 0.05 will be applied.

Data management

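### Two overlapping longitudinal models at one 0.05 level, with no visit, contrast or model named to decide the primary outcome

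*Protocol article*

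**What the plan says.** The primary outcome is the Household Outbreak Preparedness score, the mean of a cognitive and a behavioural score with equal weight (Outcome measures). It is measured at T0, T1 (immediately after the programme), T2 (one month) and T3 (three months). The Abstract describes this as: "Outcome measures will assess changes from baseline to immediately after and one- and three-month post-intervention or control".

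Statistical methods assigns two analyses to these data. A repeated-measures ANOVA evaluates change from T0 to T3 between and within the groups. A GEE is also planned: "To assess variation in results between and within the groups across the different time points", with control for potential confounders. The testing rules are "Statistical analyses will use a two-tailed test to evaluate the superiority hypothesis" and "A significance level of 0.05 will be applied". The null hypothesis is that the two arms do not differ, with no visit attached.

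On the behavioural half, the framework section says "Preparedness Behavior refers to the observable actions or practices carried out in preparation for such events". Outcome measures widens this to cover skills learned as well as practices taken up. The programme lasts one day, and participants take a booklet home and complete their household plan there (Intervention).

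**The concern.** A reader of the results needs to know in advance which number decides the trial. Here three post-baseline visits and two models could each supply it, and the article gives no order among them.

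The gap matters because results at different visits could well disagree. The Discussion itself doubts that one session will produce lasting change, so a gain at T1 that fades by T3 is foreseeable. As written, that pattern could be reported as success or as failure.

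T1 is also the visit that says least about the construct. Learned skills and cognition may have moved by then, but practices taken up by the household have had little time to do so. Because the two halves have equal weight, a cognitive gain of g with no behavioural gain still raises the primary score by g/2. The Introduction argues that awareness need not become tangible preparedness, so a conclusion resting on T1 alone would sit badly with the trial's own rationale.

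**Working it through.** **1. Does any section name the deciding contrast?** The Abstract lists three changes from baseline. The objectives, Outcome measures and the null hypothesis give no visit. Statistical methods gives two models and no ranking.

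The sample size might have identified a contrast, so I reproduced it:

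- Inputs (Sample size): z-values 1.96 and 0.842, Δ = 15.97, σ² = 138.949, n = 54, ρ = 0.048.
- Before clustering: (1.96 + 0.842)² × 2 × 138.949 / 15.97² = 8.555.
- Design effect: 1 + 53 × 0.048 = 3.544.
- Product: 8.555 × 3.544 = 30.32, against the stated 30 per arm.

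The figure reproduces, but it does not settle the question: "Δ is the mean awareness score difference between the pre- and post-assessments in the intervention group". The effect is a before-after change within one arm, not a between-arm difference at T1, T2 or T3. The article gives no between-arm difference or SD for the primary score at any visit, so power for a named contrast cannot be computed.

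**2. What does the ANOVA interaction detect?** With T0 as a level, the interaction asks whether the arm difference δ varies over the four occasions. Assuming equal variances and equal correlations, and ignoring clustering, its strength is proportional to the sum of (δ − mean δ)²:

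- Effect d at T1 only (0, d, 0, 0): mean d/4; sum = (3d/4)² + 3 × (d/4)² = 0.75d².
- Effect d sustained at T1 to T3 (0, d, d, d): mean 3d/4; sum = (3d/4)² + 3 × (d/4)² = 0.75d².

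The two are equal. The omnibus test is as sensitive to an effect that vanishes after T1 as to one that lasts three months.

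**3. What does baseline as an outcome cost?** At one follow-up visit with equal variances and baseline correlation r, the variance of a change score is proportional to 2(1 − r), and that of a baseline-adjusted score to 1 − r². The ratio is (1 − r²) / [2(1 − r)] = (1 + r)/2.

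| Assumed r | Adjusted / change variance |
|---|---|
| 0.3 | 0.65 |
| 0.5 | 0.75 |
| 0.7 | 0.85 |

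This ignores clustering. With four villages per arm, the gain also depends on the village-level baseline correlation, which is not given. The article does not say how the GEE uses the T0 score.

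**4. What if any visit could win?** Three between-arm tests (T1, T2, T3), each at two-sided 0.05:

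- Independent: 1 − 0.95³ = 14.3%.
- Simulated (one million draws) at assumed correlations of 0.3, 0.5 and 0.7: 13.6%, 12.5% and 10.9%. At 0.9 it is 8.4%.

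These count visits within one model only.

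**The case against.** The strongest defence is that the two models are not rivals. The GEE adds confounder control, so an unadjusted analysis followed by an adjusted one is a natural reading, and a condensed article may leave their ranking to an analysis plan. The part about complementary roles stands: the text is not contradictory. It does not remove the point, because this article itself commits the same comparison to two analyses at one 0.05 level and gives no rule for when they, or the visits, disagree.

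Four stronger readings are tempting, and the article does not support them:

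- **Behaviour cannot have changed by T1.** The behavioural score includes skills, and hand hygiene, CPR and preparedness planning are practised during the programme. The questionnaire items are not shown. Only the claim about adopted household practices holds. That T1 falls on the same day is itself inferred from its timing and the one-day programme.
- **The primary test treats baseline as an outcome.** This is explicit for the ANOVA only.
- **The effect is diluted to 75%.** A group main effect averaged over T0 would be (0 + 1 + 1 + 1)/4 = 0.75 of a constant effect. The article never names that main effect as its test, and its stated interest in change over time points to the interaction, which is valid.
- **The trial's type I error is 11% to 14%.** That needs an any-visit success rule, which the article does not state. A single interaction test would not carry this inflation.

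Choosing T3 over T2 is a judgement, and the article does not dictate it.

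**Conclusion.** The point holds in this form: the primary outcome has no deciding visit, contrast or model, although two overlapping analyses share one 0.05 level. The planned interaction test is valid but does not separate a transient T1 effect from a sustained one, and it is less precise than adjusting for a baseline score that is already scheduled.

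The sizes are conditional. The variance ratio of 0.65 to 0.85 assumes r of 0.3 to 0.7, a single visit and no clustering. The familywise error of about 11% to 14% assumes correlations of 0.7 to 0.3 and an any-visit rule that is neither stated nor excluded. The equal sensitivity to transient and sustained effects assumes equal variances and correlations. The missing hierarchy rests on none of these assumptions. The change should be made before results are available.

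**What to change.** In Statistical methods, name one primary analysis: the between-arm difference in the Household Outbreak Preparedness score at one visit after T1 (for example T3, the longest follow-up), from one model that accounts for village clustering, with the T0 score as covariate and only post-baseline visits as outcomes. State that the other visits, the second model and within-group changes are supportive, and that the household-preparedness conclusion will not rest on T1 alone. Align the Abstract with this.

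One related check: Data management carries the last observation forward for dropouts who cannot be contacted, so a household lost after T1 would contribute its T1 score at T3. The wording of the primary contrast should take this into account.

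The cost is wording only, since every assessment needed is already scheduled. The downside is giving up a headline claim from T1.

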## Introduction

The World Health Organization (WHO) introduced the term “Disease X” to denote a hypothetical yet potentially severe infectious disease that has not yet been identified as a cause of human disease but possesses the potential to trigger a global outbreak [1]. It is predicted to have a zoonotic origin and may be more deadly than COVID-19, imposing a significant burden on health systems, higher mortality, and major economic disruptions [2]. This impending public health threat necessitates proactive measures to mitigate its impact [3]. While eradication of future outbreaks is not realistically practicable, preparedness efforts can prevent them from escalating into health crises [4].

Preparedness strategies have been shown to be more efficient than crisis response measures in terms of limiting negative impacts, protecting human life, and mitigating financial consequences [5]. In addition, individual and household preparedness may enhance community resilience against disasters [6]. Thus, improving household preparedness is essential in managing disease outbreaks and reducing their negative impacts. However, preparedness efforts generally focus on macro-scale entities, such as healthcare systems and government bodies, often neglecting micro-scale levels like individuals, households, and local communities, who are first affected during such crises [7,8].

Preparedness programs at both community and individual levels remain limited globally. Moreover, existing initiatives tend to focus on raising awareness of diseases and natural disasters rather than implementing operational strategies to address outbreaks and emerging threats [4,7]. In Malaysia, community preparedness efforts are largely centered on flood disasters, with limited engagement of indigenous populations [9]. Existing programs primarily aim to raise awareness and reduce disease transmission risks; however, evidence suggests that such approaches do not necessarily translate into tangible preparedness outcomes [10,11]. To achieve preparedness, individuals should possess cognitive aspects of preparedness, including knowledge and positive attitudes, and should also demonstrate these through tangible behavior [12,13]. Preparedness programs should therefore not only focus on raising awareness and encouraging preventive actions but also equip individuals with guidance and skills for planning and reserving resources. Households that implement these measures may lessen the adverse impacts of health crises by enabling them to respond promptly until professional health support becomes available.

Global estimates indicate that between 50% and 92% of households are inadequately prepared for general emergencies [14]. In Hong Kong, a mere 3% of households are fully prepared for an influenza outbreak, while 41% exhibit no signs of preparedness actions [15]. There is a noticeable scarcity of data related to household outbreak preparedness in Malaysia. Local studies have noted that flood preparedness among Malaysians is relatively low, with less than half of the general public (44%) being adequately prepared and only 20% being fully prepared. Individuals primarily focus on protecting essential documents, planning for property safety, and locating the nearest evacuation facilities [16]. In contrast, flood preparedness levels in an indigenous community in Pahang are considerably lower, with 30% having property safety measures and only 10% implementing food and life-safety measures [9]. These findings indicate that both the general Malaysian population and marginalized communities exhibit inadequate preparedness levels; however, marginalized communities, especially indigenous groups, are more vulnerable and may experience more serious consequences during outbreaks, particularly with the threat of Disease X [17].

Indigenous communities in Malaysia are referred to as “Orang Asli.” Selangor has the third-largest Orang Asli population in Malaysia, consisting of 74% Proto-Malays ethnicity, with Temuan being the largest sub-ethnic group [18]. Numerous outbreaks of infectious diseases have affected the Orang Asli community, with many instances documenting cases of fatalities [19,20]. The higher risk of outbreaks among the Orang Asli can be attributed to various factors such as lower education levels, inferior socioeconomic status, poor living conditions, malnutrition, lower vaccine coverage, healthcare barriers, cultural challenges, and societal marginalization [9,19]. Preventive measures in Orang Asli communities have also been reported as inadequate [20].

Many Orang Asli villages in Selangor are located in deforested areas, and many continue to rely on the forest for their livelihood [9,18,19]. Therefore, the risk of human-wildlife contact cannot be discounted, emphasizing the need for targeted interventions for this group. Moreover, Selangor is one of the country’s most densely populated states, creating an additional threat. This setting increases the potential for rapid disease transmission beyond the Orang Asli villages, potentially leading to larger outbreaks and higher mortality rates if not effectively addressed. The COVID-19 pandemic demonstrated this impact when Selangor experienced the highest number of cases and fatalities attributable to its densely populated environment [21].

Considering these factors, the Orang Asli community in Selangor is highly vulnerable to severe impacts from outbreaks and novel threats such as Disease X. Targeted interventions are needed to improve their household preparedness, enabling them to reduce impacts while awaiting control measures from health authorities. Research-based evaluation of these interventions is essential to justify resource investment and support for marginalized groups and to propose adaptations for other communities and nationwide implementation to stakeholders.

To the best of our knowledge, there are no published studies that have examined tailored household preparedness interventions for outbreaks or Disease X among marginalized communities. This paper presents the research protocol for X-SIAGA (KesiapSIAGAan Penyakit X dan Wabak), an intervention package designed to enhance household preparedness for Disease X and potential outbreaks among the Orang Asli communities in Selangor, Malaysia. The trial will evaluate the effectiveness of the X-SIAGA intervention, in addition to standard educational brochures, compared with educational brochures alone, in improving household preparedness within this population.

The proposed hypotheses for this study are: (i) Hypothesis 1 (H1): The intervention changes household preparedness levels, potentially improving their capability to respond to Disease X and potential outbreaks; (ii) Hypothesis 2 (H2): The intervention changes cognitive aspects related to preparedness, improving knowledge and attitudes, including health beliefs, toward Disease X and outbreaks; and (iii) Hypothesis 3 (H3): The intervention changes behavioral aspects related to preparedness, enhancing skills and tangible preparedness practices among households for Disease X and outbreak preparedness.

To test the hypotheses, the objectives established for this study are as follows: (i) to assess the effectiveness of the intervention package on the level of *Household Outbreak Preparedness* among the Orang Asli in Selangor (primary outcome); (ii) to assess the effectiveness of the intervention package on the level of *Cognitive Preparedness *among the Orang Asli in Selangor (secondary outcome); and (iii) to assess the effectiveness of the intervention package on the level of *Preparedness Behaviour *among the Orang Asli in Selangor (secondary outcome).

